## Abstract

**Background:**

Immunosuppression in transplantation continues to be associated with a multitude of adverse effects. Induction of immune tolerance may be a viable strategy to reduce dependence on immunosuppression. Various trials are currently underway to assess the efficacy of this strategy. However, long-term safety data for these immune tolerance regimes has yet to be established.

**Methods/design:**

At the completion of primary follow-up of various Medeor kidney transplant studies, subjects receiving cellular immunotherapy products will be followed annually as per protocolized schedule for up to an additional 84 months (7 years) to evaluate long-term safety. Long-term safety will be assessed by summarizing incidence of serious adverse events, adverse events leading to study withdrawal and hospitalization rates.

**Discussion:**

This extension study will be an important step in evaluating safety issues pertaining to immune tolerance regimens, long-term effects of which are largely unknown. These data are essential for furthering an unrealized goal of kidney transplantation- graft longevity without the adverse effects from long-term immunosuppression. The study design utilizes the methodology of a master protocol, wherein multiple therapies can be assessed simultaneously with accompanied gathering of long-term safety data.

## Background

Thefield of transplantation is actively engaged in studying the induction of effective immune tolerance without the use of immunosuppression. Clinical trials to establish tolerance are using a combination of organ and hematopoietic cell transplantation to achieve immunological tolerance via either full or mixed donor chimerism [1–3]. Full donor chimerism is acquired when the entire recipient hematopoietic system is replaced by donor cells (donor cells > 98%) resulting in deactivation of donor T cells [4]. Mixed chimerism is defined as continued mixing of donor and recipient hematopoietic cells in recipient tissues after transplantation of donor cells. Achievement of mixed chimerism can result in tolerance of organ grafts from the hematopoietic cell donors without the need for immunosuppression [3]. Various centers have employed myeloablative or non-myeloablative conditioning strategies, with total body, local thymic, or lymphoid irradiation, and subsequent donor whole bone marrow transplantation or infusion of granulocyte colony stimulating factor (G-CSF) mobilized CD34 + T cells [5–7]. Establishment of mixed chimerism is associated with lower risk of graft versus host disease (GVHD) and immunodeficiency in comparison to full donor chimerism. The Stanford group reported the long-term outcomes of a pioneering, single-center study in which kidney transplant recipients were given post-transplant conditioning with 10 doses of total lymphoid irradiation (TLI) and 5 doses of anti-thymocyte globulin (ATG) [3]. On completion of TLI, a combination of enriched CD34 + hematopoietic progenitors and a defined number of donor T cells were injected immediately (G-CSF was administered to donors to mobilize progenitors into the blood such that collection was performed via apheresis). Fully HLA-matched patients were given T cells along with the CD34 + cells. The majority of the patients (24/29 fully HLA matched) achieved mixed chimerism for at least 1 year. In the mixed chimerism group, MMF was withdrawn 39 days after cell infusion following kidney transplantation, while calcineurin inhibitors were tapered beginning at approximately 6 months and ceased after approximately 1 year. In the Stanford study, 23/24 (96%) had no evidence of rejection in the first year after withdrawal of immunosuppression. Although two late rejections occurred at 44 and 60 months after rejection, no grafts were lost due to rejection [8]. For this strategy to achieve success, it is imperative to elucidate the long-term safety profile. The monitoring of events such as rejection, graft dysfunction/loss, graft vs host disease (GVHD), and opportunistic infections is important. The MDR-105-SAE study is designed to be a long-term safety monitoring extension trial involving Medeor’s cellular immunotherapy administered to kidney transplant recipients to induce immune tolerance via mixed lymphohematopoietic chimerism. MDR-105-SAE is a Master Protocol that is designed to allow current and future kidney transplant studies to enroll into a single design where safety data can be analyzed in a consistent manner. The initial clinical trial to be enrolled is a phase 3 open label, multicenter, randomized controlled trial to assess safety and efficacy of donor-derived CD34 + hematopoietic stem/progenitor cells and a specified dose of CD3 + T cells administered to recipients of HLA-matched, living donor kidney transplants post total lymphoid irradiation (TLI) and rabbit-anti-thymoglobulin induction, with progressive tapering of maintenance immunosuppression (NCT03363945).

This study protocol will provide up to 84 months (7 years) of additional follow-up to collect the data into a centralized database allowing for continuous monitoring of any important safety signals.

## Methods

### Patient population

The study population will consist of kidney transplant recipients who received Medeor’s cellular immunotherapy in its previous and future kidney transplant studies. Upon completion of the initial study, the kidney transplant recipients who received the Medeor product are given an option to participate in the long-term follow-up study, MDR-105-SAE. Study participants with subsequently failed allografts, albeit now on kidney replacement therapy, will also be included in this study. The study will exclude subjects who have lost kidney allografts and have been subsequently retransplanted.

#### Subject inclusion criteria

All of the following criteria must be met for study participants to be included in the study:Able and willing to fully comply with all study procedures and restrictions.Able to understand and provide written, signed, and dated informed consent to participate in the study in accordance with International Council for Harmonization (ICH) Good Clinical Practice Guidelines (GCP) and all applicable local regulations.Have previously completed a Medeor study and received a Medeor cellular immunotherapy product

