#### Subject exclusion criteria

Participants who meet any of the following criteria will not be eligible:Has any condition or circumstance, which in the opinion of the investigator would significantly interfere with the subject’s protocol compliance or put the subject at increased risk. The subject will be expected to comply with all study visits and procedures. The protocol requires annual study visits where a complete physical exam, vital signs, and laboratory samples will be obtained.Unable or unwilling to provide written, signed, and dated informed consent to participate in the study.Has undergone a second organ transplant with an organ derived from an individual other than the donor of the transplant kidney received during a Medeor study

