### Discontinuation and withdrawal

Withdrawal of individual subject(s)

A subject is free to withdraw from the study at any time without giving reason for doing so and without penalty or prejudice. The investigator is also free to terminate a subject’s involvement in the study at any time if a subject’s clinical condition warrants it.

Subjects who withdraw all consent for further participation in the study will be withdrawn from all follow-up assessments and will only be followed for mortality through public records. Subjects should have an end of the study visit completed shown in Table 1 at the time of their discontinuation.(2)Discontinuation of the site

If an investigator intends to discontinue participation in the study, the investigator must.immediately inform the sponsor. The sponsor will provide written notice for sitetermination.(3)Discontinuation of the study

The sponsor may terminate this study prematurely, either in its entirety or at any study site, for reasonable cause provided that written notice is submitted in advance of the intended termination. If the sponsor terminates the study for noncompliance reasons, the sponsor will immediately notify the investigators and subsequently provide written instructions for study termination.

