### Safety parameters

Vital signs

All recipients will have vital signs (systolic and diastolic blood pressure, pulse, respiratory rate, and temperature) collected at all yearly study visits. After the subject has been sitting for 5 min, with back supported and both feet placed on the floor, systolic and diastolic blood pressure will be measured with an appropriately sized cuff and calibrated machine.(b)Physical examination

A complete physical examination will be performed on all recipient subjects as part of the annual safety evaluation study visits. Significant findings that are present prior to signing the Informed Consent Form must be included in the Medical History screen on the subject’s case report form (CRF). The investigator or a qualified designee will conduct the exams, determine findings, and assess any abnormalities as to clinical significance.

(c)Laboratory assessments

Clinical laboratory tests, including hematology and comprehensive metabolic panel (chemistry), will be performed on recipients as specified in the Schedule of Assessments and Procedures in Table 1. Clinical laboratory tests are to be performed and reviewed by the investigator or qualified designee:Hematology: complete blood count (CBC) with differential will be measured locally for recipients annually.Blood chemistry (Comprehensive Metabolic Panel): A Comprehensive Metabolic Profile must include all of the following measurements: blood urea nitrogen (BUN), creatinine, sodium, potassium, chloride, bicarbonate, glucose, phosphorus, total protein, albumin, creatine kinase (CK), lactate dehydrogenase (LDH), amylase, and liver chemistries including total and direct bilirubin, alanine aminotransferase (ALT), aspartate aminotransferase (AST), and alkaline phosphatase (ALP). The full chemistry panel will be analyzed locally using accepted laboratory methodology at each of the yearly visits.Urinalysis: Instances of proteinuria and/or microscopic hematuria will be recorded.

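### In a no-treatment safety study, exclusion and termination on health grounds can selectively lose higher-risk recipients, so late harm is liable to be understated

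*Protocol article*

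**What the plan says.** All references are to the protocol article.

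- **Nature of the study.** Study design says that no treatment is given. Treatments calls the study strictly observational and names annual chimerism testing, in those who keep mixed chimerism, as the only monitoring beyond standard care.
- **Who enters.** Patient population opens: "The study population will consist of kidney transplant recipients who received Medeor’s cellular immunotherapy in its previous and future kidney transplant studies". Its next sentence offers participation once the initial study is complete, and the Subject inclusion criteria require recipients to "Have previously completed a Medeor study and received a Medeor cellular immunotherapy product". Recipients with failed grafts on kidney replacement therapy are kept. Retransplanted recipients are not: "The study will exclude subjects who have lost kidney allografts and have been subsequently retransplanted".
- **Discretion at entry.** The Subject exclusion criteria bar anyone with a condition or circumstance that, in the investigator's opinion, "would significantly interfere with the subject’s protocol compliance or put the subject at increased risk". The same criterion refers to attendance at annual visits with examination and laboratory samples.
- **Discretion at exit.** Discontinuation and withdrawal says: "The investigator is also free to terminate" a subject's involvement when the clinical condition calls for it. An end-of-study visit is expected. Mortality follow-up through public records is stated only for those who withdraw all consent.
- **After exit.** Monitoring and reporting serious adverse events only says that early discontinuers are encouraged to return, and that information may be obtained from physicians or records.
- **Start of recording.** Study visits and procedures sets entry within 3 months of parent-study completion. In Table 1, SAE and outcome recording is blank at visit 0 and begins after enrollment. Hospitalizations since transplant are recorded from visit 1.
- **Use of the data.** Statistics summarizes the incidence of SAEs, AEs leading to withdrawal and hospitalization rates, and the number and proportion of subjects with each outcome of special interest.

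**The concern.** A risk-based exclusion or a stop for clinical condition normally protects a subject from a study treatment. Here there is none to withhold, so these clauses mainly decide who is observed, and they can act on health after the product was given. A recipient who is deteriorating may be kept out at entry or dropped later, and the events that follow may never reach the database.

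Long-term safety is the study's only question, and late malignancy, MDS, GvHD and death are what a follow-up of up to 84 months is meant to detect. If those lost are at higher risk, the reported incidence is too low. No later analysis can recover people who never enrolled or events that were never collected.

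**Working it through.** The article states no sample size, event rate, non-completion share or withdrawal rate, so there is no figure to reproduce. The check has three parts.

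**1. What the text secures for each route of loss**

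| Route | What the text provides | What can be lost |
|---|---|---|
| Not entered because judged at increased risk | Nothing | All events in the extension period |
| Participation ended by the investigator | End-of-study visit; open SAEs followed to recovery or stabilization; return encouraged; outside records may be used | New SAEs, outcomes and death after exit |
| All consent withdrawn | Mortality through public records | Everything else, which is the subject's right |
| Event between parent-study end and enrollment | Hospitalizations since transplant | Other SAEs and outcomes; a recipient who dies in the gap never enrolls |

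Vital status after exit is thus specified for a subject who withdraws all consent, but not for one whose participation the investigator ended.

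**2. Direction and possible size at entry (illustration only)**

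Let p be the incidence in those observed, f the share of recipients lost and RR their risk relative to those observed. Then:

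- incidence in all recipients = (1 − f) × p + f × RR × p = p × (1 − f + f × RR)
- observed / full = 1 / (1 − f + f × RR)

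Both f and RR are assumptions. Observed / full is:

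| f | RR 0.5 | RR 1 | RR 1.5 | RR 2 | RR 3 |
|---|---|---|---|---|---|
| 5% | 1.026 | 1.000 | 0.976 | 0.952 | 0.909 |
| 10% | 1.053 | 1.000 | 0.952 | 0.909 | 0.833 |
| 20% | 1.111 | 1.000 | 0.909 | 0.833 | 0.714 |

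- f = 10%, RR = 2: 1 / (0.90 + 0.20) = 1 / 1.10 = 0.909. An observed 20% would correspond to 0.20 × 1.10 = 22% in all recipients.
- f = 20%, RR = 3: 1 / (0.80 + 0.60) = 1 / 1.40 = 0.714. An observed 20% would correspond to 0.20 × 1.40 = 28%.

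**3. Exits and the entry gap**

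A subject who leaves after entry contributes events until then. For rates, f is therefore the share of follow-up time lost, which is smaller than the share of people. If 10% were ended at year 4 of 7 (an assumption), f = 0.10 × 3/7 = 0.043. With RR = 2, the ratio is 1 / (1 + 0.043) = 0.959. This supposes that the analysis allows for unequal follow-up, which is a matter for the SAP.

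The gap is at most 3 of 84 months, 3/84 = 3.6%. That is a share of time, not a bias: starting both events and time at enrollment does not by itself lower a rate.

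**The case against.** The case on the other side is substantial. This is openly a roll-over study of completers. The exclusion also covers compliance and, like termination, permits removal without requiring it. Failed grafts stay in, and so do subjects who restart immunosuppression. The AE that leads to withdrawal is itself counted, an end-of-study visit is expected, open SAEs are followed, and records may be used after exit. The study is descriptive, and its results validly describe those enrolled. The full protocol may say more.

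Most of that stands, and it rules out several stronger readings that a reader might infer:

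- **That the inclusion criterion contradicts Patient population.** The opening sentence of that section sets no completion condition, but the next one does, and Study design and Study visits and procedures agree with it.
- **That the sickest recipients, including those with graft failure, are removed.** Failed grafts on replacement therapy are expressly eligible. The article does not define completion of a parent study, and recipients may leave one for reasons unrelated to health.
- **That illness is all the exclusion can select on.** It also covers circumstances and compliance.
- **That SAEs in the entry gap are turned into medical history.** The sentence "Significant findings that are present prior to signing the Informed Consent Form must be included in the Medical History screen" stands under physical examination and concerns findings present before consent. Baseline characteristics also records clinical course.
- **That harm is understated by a known amount, such as 9% to 29%.** Those figures are 1 − 0.909 and 1 − 0.714, and they rest entirely on assumed inputs.

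What the objection does not remove is this: the safeguards after exit are optional, none reaches a recipient kept out at entry, and the clauses have little protective purpose without a study treatment. These are stated rules, not details left to another document.

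**Conclusion.** The point holds as a risk of bias, not as a demonstrated understatement. The increased-risk exclusion and termination for clinical condition permit selective loss of higher-risk recipients. Optional follow-up after exit and the late start of SAE and outcome recording add to it. The incidence of SAEs and late outcomes is therefore liable to be too low.

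The text is clear. The direction rests on the assumption that those lost are at higher risk (RR above 1); at RR = 1 there is no bias, and below 1 incidence would be overstated. The size is unknown. The tabulated ratios for RR above 1, 0.976 down to 0.714, show only what assumed inputs would give. Hospitalization is the measure least exposed to the entry gap. Separately, restriction to parent-study completers is a declared design choice: it limits whom the results describe and is not in itself an error.

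**What to change.** 1. **Subject exclusion criteria:** delete the increased-risk clause or limit it to risk from the study's own procedures. Allow remote or records-only follow-up for recipients who cannot attend.
2. **Discontinuation and withdrawal, and Monitoring and reporting serious adverse events only:** state that a subject whose visits the investigator ends stays in records-based follow-up for SAEs, outcomes of special interest and death unless consent is withdrawn.
3. **Table 1, visit 0:** collect SAEs and outcomes from the parent-study last-visit date, which Baseline characteristics already captures.
4. **Reporting:** give the number of all product recipients, with reasons for non-entry (non-completion, retransplantation, investigator's judgement, refusal) and for exit. State that the results apply to completers, unless consenting non-completers are also admitted. Admitting them is a design decision for the sponsor.

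These changes govern observation only; treatment decisions stay with the treating physicians. The cost is a protocol amendment, some record retrieval, and thinner data for records-only subjects. Acting early matters because follow-up that is not collected may not be recoverable.

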#### Subject exclusion criteria

Participants who meet any of the following criteria will not be eligible:Has any condition or circumstance, which in the opinion of the investigator would significantly interfere with the subject’s protocol compliance or put the subject at increased risk. The subject will be expected to comply with all study visits and procedures. The protocol requires annual study visits where a complete physical exam, vital signs, and laboratory samples will be obtained.Unable or unwilling to provide written, signed, and dated informed consent to participate in the study.Has undergone a second organ transplant with an organ derived from an individual other than the donor of the transplant kidney received during a Medeor study

### Baseline characteristics

Participant demographics, past medical history, and clinical course will be recorded. To be able to link the subject data from this study to the parent study, the study code, center number, subject number, and the last visit date from the parent study will be recorded in the case report form (CRF).

### Study design

At the time of enrolment in the initial study, the kidney transplant recipients are asked to acknowledge the expectation to participate in a multi-year, long-term follow-up study at the completion of the observation period in the initial study. Upon completion of the initial study, the kidney transplant recipients who received the Medeor product will sign the consent form and begin Study MDR-105-SAE. These patients are expected to participate in the MDR-105-SAE study. Medeor is working with the sites to be able to enroll these subjects into the MDR-105-SAE study upon completion of the initial study. At the completion of primary follow-up of various Medeor kidney transplant studies (called parent studies), subjects receiving Medeor’s cellular immunotherapy products will be followed annually for up to an additional 84 months (7 years) for long-term safety evaluation. No study treatment is involved. All immunosuppression and therapeutic drug monitoring will be managed by treating physicians according to local standard of care (SOC). Any changes in, and reinstitution of immunosuppression drug therapy, will be at the treating physician’s discretion. Post-kidney transplant biopsy will be performed for cause at any time at the discretion of a subject’s treating physician. MDR-105-SAE protocol assessments will be performed annually following study entry. All participants must provide informed consent prior to enrolling into the MDR-105-SAE study.

### Study visits and procedures

Within 3 months of completion of a Medeor clinical trial, the kidney transplant recipients who received a Medeor cellular immunotherapy product will begin annual study MDR-105-SAE visits at 12 months (with an allowed deviation of ± 1 month for scheduled annual visits).

Unscheduled study visits at the transplant center and at other health care delivery facilities may occur. Records from such visits would be obtained and reviewed for adequate safety reporting.

Extensions in study visit scheduling to accommodate non-working days will not be considered protocol deviations. Additionally, extensions in scheduling because of special circumstances, such as subject work issues, lack of transportation, and bad weather, if cleared in advance with the medical monitor, will also not be considered protocol deviations.

The schedule for clinical assessments is elucidated in Table 1 (below references).

**Table 1 Tab1:** Schedule of monitoring over the course of MDR-105-SAE

**Study visit year**	1		2	3	4	5	6	7
**Study visit number**	0	1	2	3	4	5	6	7
**Study visit window (months)**	+ 3	± 1	± 1	± 1	± 1	± 1	± 1	± 1
**Assessment**	**Screening**	**Post enrollment**						
Informed consent	⦁							
Confirm study eligibility criteria	⦁							
Demographics	⦁							
Baseline characteristics	⦁							
Medical history	⦁							
Prior/concomitant medication	⦁	⦁	⦁	⦁	⦁	⦁	⦁	⦁
Perform complete physical examination	⦁	⦁	⦁	⦁	⦁	⦁	⦁	⦁
Record vital signs	⦁	⦁	⦁	⦁	⦁	⦁	⦁	⦁
Record weight	⦁	⦁	⦁	⦁	⦁	⦁	⦁	⦁
Record height	⦁							
Hematology panel^a^		L	L	L	L	L	L	L
Comprehensive metabolic panel^a^		L	L	L	L	L	L	L
Urinalysis		L	L	L	L	L	L	L
Calcineurin inhibitor trough levels^b^		L	L	L	L	L	L	L
Mixed chimerism testing^c^		C	C	C	C	C	C	C
Record instances of acute rejection requiring treatment		⦁	⦁	⦁	⦁	⦁	⦁	⦁
Record instances of proteinuria		⦁	⦁	⦁	⦁	⦁	⦁	⦁
Kidney biopsy^d^		Only for cause						
Complete subject status form		⦁	⦁	⦁	⦁	⦁	⦁	⦁
Record all SAEs		⦁ (ongoing)						
Record AEs leading to study withdrawal		⦁ (as needed)						
Record history of hospitalizations since transplant		⦁	⦁	⦁	⦁	⦁	⦁	⦁
Record development of NODAT^e^		⦁	⦁	⦁	⦁	⦁	⦁	⦁
Record development of GVHD		⦁	⦁	⦁	⦁	⦁	⦁	⦁
Record instances of BK viremia development		⦁	⦁	⦁	⦁	⦁	⦁	⦁
Record instances of dnDSA		⦁	⦁	⦁	⦁	⦁	⦁	⦁
Record instances of cardiovascular events^f^		⦁	⦁	⦁	⦁	⦁	⦁	⦁
Record instances of opportunistic infection		⦁	⦁	⦁	⦁	⦁	⦁	⦁
Record instances of PTLD/other malignancies		⦁	⦁	⦁	⦁	⦁	⦁	⦁
Record instances of MDS		⦁	⦁	⦁	⦁	⦁	⦁	⦁

*AE* adverse effects, *C* central laboratory, *dnDSA* de novo DSA, *L* local laboratory, *MDS* myelodysplastic syndrome, *NODAT* new-onset diabetes after transplantation, *PTLD* post-transplant lymphoproliferative disease

^a^Testing will be completed at each follow-up visit and will be analyzed locally using accepted laboratory methodology

^b^For subjects who have discontinued CNI, compliance check is performed as needed to assess trough levels locally, per standard accepted laboratory methodology. CNI trough levels will be assessed in all recipients at each follow-up visit for subjects taking CNI

^c^The degree of donor chimerism in recipient blood will be by central laboratory. Subjects who have lost mixed chimerism (< 5%) do not need to repeat testing at subsequent visits

^d^Transplant kidney biopsy will be performed for cause at the discretion of a subject’s treating physician and will undergo local pathology review

^e^NODAT will be determined based on need for use of an antidiabetic agent for more than 30 days, or 2 fasting plasma glucose levels ≥ 126 mg/dL in a subject who was not diabetic at study entry

^f^Cardiovascular events include acute myocardial infarction, stroke, acute peripheral arterial occlusion, and revascularization procedure

